### Patient follow-up

Information on prognostic status is collected via follow-up till 3 years after the last treatment. Follow-up will be conducted on a 3-month basis in the first two years and every half-year in the third year. In each follow-up, participants receive physical examinations (i.e. height, weight, KPS, routine examination of heart/lung/abdomen), laboratory tests (including blood cell test, blood biochemical test, and serum tumor marker test), imageological examinations (including ultrasonography [every 3 months], enhanced CT/MRI [every 6 months], endoscopy [every 12 months], and chest radiograph). Tumor assessment will be conducted if recurrence is suspected, and further treatment such as surgery or chemotherapy will be administered when needed and will be recorded in the case report form. To promote participant retention and complete follow-up, three attempts will be made to contact and remind the participants to come to the hospital for follow-up, and their transportation fee will be covered by the research project.

### Statistical analysis

On the basis of prior research, the conventional open surgery group is expected to have a 30-day postoperative complication rate of 35%. After the repeated discussion among investigators, a consensus was reached that a 19% decrease in the complication rate was considered as superiority of laparoscopic gastrectomy over conventional open approach. PASS software returned a sample size of 164 (82 per arm) is planned, with a type I error of 0.05 (two-sided) and a statistical power of 80%. The total sample size needed is 180 (90 per am) after taking into account of a 10% dropout rate.

Data analysis will be performed on both intention-to-treat and per-protocol basis. Outcome data obtained from all participants will be included in the intention-to-treat analysis, regardless of protocol adherence; whereas in the per-protocol analysis, data of non-adherers will be excluded. For variables with a significant amount of missingness, multiple imputations will be conducted for the purpose of sensitivity analysis. Of the clinical and pathological characteristics, categorical data will be presented as number and percentage and continuous variables as mean and standard deviation if normally distributed or as median and range if otherwise. The primary analysis in this study aims to compare the between-group difference in 30-days postoperative complication rate, reoperation rate, readmission rate, and mortality rate. Pearson’s Chi-squared tests or Fisher’s Exact tests, as appropriate, will be performed for this purpose. For the continuous variables of secondary outcomes, this will be done by independent samples t-tests or Mann-Whitney U tests, as appropriate. The overall survival curves will be constructed as time-to-event plots using the Kaplan–Meier method. Log-rank tests will be used to make a simple comparison of the survival curves. Disease-free survival will be analyzed in the same manner. Proportional hazard Cox regression adjusted for variables will be employed when necessary. Subgroup analyses will be conducted by G8 score, age group, TNM stage, tumor location, laparoscopy-assisted or total laparoscopic gastrectomy, distal or total gastrectomy, and comorbidities status. All statistical analyses will be conducted in standard statistical software such as SAS and STATA with a significance level of 0.05 (two-sided).

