## Background

Gastric cancer is one of the most common cancer and cause of cancer death in China and worldwide [1]. With the rapid aging of global population, the number of elderly patients with local advanced gastric cancer has been continuously increasing. Surgery is the essential treatment for local advanced gastric cancer. However, elderly patients are at high risk of postoperative complications due to reduced functional reserve and increased comorbidities. Studies have shown that elder patients can have postoperative complication incidence up to 18–32% and surgery-related mortality rate to 3.8–9.5% [2–4]. Therefore, elderly patients usually require more restrict operative injury control compared to the younger population. Surgical safety and effectiveness has become a crucial research focus for local advanced gastric cancer among elderly patients.

Laparoscopic gastrectomy is one of the standard treatments for early gastric cancer and has demonstrated its application value in local advanced gastric cancer [5–7]. Two recent meta-analysis on observational studies have shown the feasibility of laparoscopic gastrectomy in elderly gastric cancer patients [8, 9]. Compared to conventional open resections, elderly patients may benefit from the advantages of laparoscopic approach such as less trauma, less blood loss, faster bowel movement recovery, earlier food intake, and shorter hospitalization. However, laparoscopic gastrectomy raises issues such as prolonged operation time and disturbance of circulatory and respiratory dynamics by carbon dioxide pneumoperitoneum during the procedure [10]. Nonetheless, all currently available evidence comes from observational studies that are susceptible to bias and evidence on long-term survival is scarce. We therefore proposed to conduct this randomized controlled trial comparing the feasibility and survival benefit of laparoscopic with open gastrectomy for elderly patients with local advanced gastric cancer.

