### Study design, setting, and participant

This is a prospective, randomized, single-center, open-label phase II trial, which takes place in the Gastrointestinal Cancer Center of Peking University Cancer Hospital and Institute, China (Fig. 1). Adult ambulatory patients aged 70 and above, with Karnofsky Performance Status (KPS) ≥ 70, histology proved gastric cancer, cT2-4aNanyM0 (UICC TNM staging 7th edition), and no prior cancer treatment, will be screened for inclusion and exclusion criteria (Table 1) by the reception oncologist. Eligible patients will be invited for study participation at their first visit at the Gastrointestinal Cancer Center. The doctor who sees the patient will give a formal and detailed description of the study and its procedures. Upon the acquisition of patient written informed consent form, patients will undergo oncology evaluation (e.g. abdominal enhanced CT and/or MRI scan, chest plain scan CT, cervical lymph node, ultrasonography, pelvic ultrasonography/CT, serum tumor markers, laparoscopic exploration and free cytological examination of peritoneal cavity) as well as geriatric assessment with G8 screening tool. Patients will afterwards be randomized 1:1 to either laparoscopic or open surgery arm by the data manager in the team using random number table. None of patients, surgeons, or data analysts will be blinded.

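### The sample size is right for 35% v 16%, but the 80% power depends on an unexplained 35% open-arm rate and on a 19% decrease that is really 19 percentage points; covariate adjustment is a cheap safeguard

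*Protocol article*

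**What the plan says.** All the design inputs are in the protocol article, under Statistical analysis.

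- Control rate: "the conventional open surgery group is expected to have a 30-day postoperative complication rate of 35" per cent. It is attributed to prior research, with no reference at that point.
- Effect: "a 19% decrease in the complication rate was considered as superiority of laparoscopic gastrectomy over conventional open approach". This was agreed among the investigators. The text does not say whether it is absolute or relative.
- Size: "PASS software returned a sample size of 164 (82 per arm) is planned". Alpha is set at 0.05, two-sided, and the power target is 80%.
- Dropout: "The total sample size needed is 180 (90 per am) after taking into account of a 10% dropout rate".
- Test for the primary comparison: an unadjusted Pearson chi-squared or Fisher's exact test.

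The Background gives the only other complication figure for this age group: "elder patients can have postoperative complication incidence up to 18–32" per cent. The article does not connect the two figures.

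**The concern.** The design rate lies above the top of the only range that the article quotes, and nothing explains the gap. The effect is also easy to misread: a 19% decrease sounds modest, but the calculation needs complications to fall by more than half. If the true open-arm rate is lower than 35% and the treatment works proportionally, the trial has less than 80% power. The article presents the trial as support for a later multicentre phase III study. A non-significant result from an underpowered comparison could then be read as no benefit and discourage that study.

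**Working it through.** **Inputs.** Open rate 35%, decrease 19%, two-sided alpha 0.05, power 80%, 82 per arm, 180 randomised and 10% dropout (all Statistical analysis); 1:1 allocation (Study design, setting, and participant); 18–32% (Background).

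**Step 1: reproduce the stated size.** Two proportions, pooled variance under the null, no continuity correction:

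n = [1.960·√(2·p̄·(1−p̄)) + 0.8416·√(p₁(1−p₁) + p₂(1−p₂))]² / (p₁−p₂)²

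With p₁ = 0.35, p₂ = 0.16 and p̄ = 0.255:

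n = (1.960·0.6164 + 0.8416·0.6016)² / 0.19² = 2.939 / 0.0361 = 81.4, so 82 per arm.

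This matches. Power at 82 per arm is 80.3%.

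**Step 2: absolute or relative?** A 19% relative decrease gives p₂ = 0.35 × 0.81 = 0.2835, and the same formula gives 767.05, so 768 per arm. Only the absolute reading fits. The implied relative reduction is 19/35 = 54.3%, a risk ratio of 0.16/0.35 = 0.457.

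**Step 3: power at lower open rates.** Power = Φ{[|p₁−p₂|·√n − 1.960·√(2·p̄·(1−p̄))] / √(p₁(1−p₁) + p₂(1−p₂))}.

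Example with the risk ratio held at an open rate of 32%: p₂ = 0.1463, p̄ = 0.2331, n = 82. This gives (0.1737·9.055 − 1.960·0.5980)/0.5852 = 0.685, and Φ = 75.3%.

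| Open rate | Risk ratio 0.457 held, 82 per arm | Same, 90 per arm | 19 points held, 82 per arm | n per arm for 80% (risk ratio held) |
|---|---|---|---|---|
| 35% | 80.3% | 83.8% | 80.3% | 82 |
| 32% | 75.3% | 79.2% | 83.6% | 92 |
| 25% | 61.6% | 65.7% | 92.7% | 126 |
| 18% | 45.7% | 49.3% | impossible | 187 |

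Holding 19 points means a relative reduction of 19/32 = 59% at 32% and 19/25 = 76% at 25%. At 18% the laparoscopic rate would be negative. Exact enumeration of the chi-squared test at 82 per arm, risk ratio held, gives 46.0% at 18% and 76.2% at 32%, so the normal approximation is not driving the result.

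**Step 4: dropout.** 180 × 0.9 = 162 evaluable, 81 per arm, with power 79.8% against 80.3% at 82 per arm. Keeping 164 evaluable needs 164/0.9 = 182.2, so 183. The difference is half a percentage point of power.

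**Step 5: what adjustment would have to deliver.** If adjustment removes a fraction r of the variance, 82 patients act roughly like 82/(1−r). With the risk ratio held, returning to 80% needs r ≈ 1 − 82/92 = 11% at an open rate of 32%, and 1 − 82/126 = 35% at 25%. The documents give no figure for how well age, G8 and stage predict complications, so the gain cannot be computed from them.

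**The case against.** A reader might infer from the Background range that true power is simply 46–75%. The documents do not support this, for four reasons.

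- **The effect scale is a choice.** The protocol fixes a difference of 19 points, not a risk ratio. Holding the difference, power rises as the open rate falls. That reading becomes demanding at 25% and fails at 18%, so it does not cover the range, but the risk-ratio reading is still an assumption.
- **The ranges may not be comparable.** The Background does not tie its figure to open surgery, locally advanced disease or 30 days. The trial's own list of complications is broad and sets no minimum Clavien-Dindo grade, which could raise the rate.
- **The population could go either way.** Excluding patients with poor cardiac, pulmonary or renal function may lower the rate. Age 70 and above, cT2–4a disease and total gastrectomy may raise it. No figure in the article settles the net direction.
- **82 evaluable may be pessimistic.** The endpoint is at 30 days and surgery follows within a week of randomisation. With 90 per arm and the risk ratio held, power at 32% is 79.2%.

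These points stand, and they rule out calling the 80% an error or the two figures a contradiction. They do not explain why 35% was chosen over a rate within the quoted range, and they do not remove the ambiguity in the stated decrease.

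**Conclusion.** The calculation is correct for its inputs. What holds is narrower: the 35% is unexplained beside the Background figure, and the required effect is 19 percentage points, a 54% relative reduction, which the wording hides. With the risk ratio fixed at 0.457, power at open rates of 32%, 25% and 18% is 75%, 62% and 46% with 82 per arm evaluable, or 79%, 66% and 49% with 90. With the 19-point difference fixed, it is above 80% at 32% and 25%. The stated 80% is therefore conditional on the 35% rate and the 16% target. The dropout discrepancy is real but negligible.

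**What to change.** **Main change, enrolment unchanged.** Replace the unadjusted chi-squared test for the primary complication comparison with an analysis adjusted for prespecified baseline variables already collected: age, G8 score and clinical stage. Report a standardised risk difference with its confidence interval. Use clinical rather than pathological stage, so that every covariate predates surgery. The gain is likely modest and should not be presented as restoring 80% power at the lower open rates. The cost is slightly more analysis work and wording that fixes the covariates before outcome data are compared.

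**Wording changes, at no cost beyond editing.**

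- Write the effect as 19 percentage points (35% to 16%).
- State that 80% power is conditional on the 35% open rate, and explain how that rate relates to the 18–32% in the Background. Show power over 18–35% with the effect scale stated. The stated power will look less secure.
- Correct the dropout sentence: 180 less 10% is 162 evaluable, about 79.8% power.

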**Methods:**

The current study has a randomized, parallel controlled, single-center, open-label, superiority design with two arms. A sample of 180 local advanced gastric cancer patients aged 70 and above will be recruited in Peking University Cancer Hospital and Institute. Participants will be randomized to either receive open or laparoscopic gastrectomy. The primary outcome is surgical safety, including complication rate, reoperation rate, readmission rate, and mortality rate within 30 days after surgery. The secondary endpoints include postoperative rehabilitation status, one-year postoperative life quality, three-year overall and disease-free survival. Assessments will take place at baseline (before random assignment), at 30 days, one-year, and three-year after the surgery. The study has been approved by an ethical review board.

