For those receiving laparoscopic gastrectomy, the case will be required to be converted to open surgery if one of the following happens: confluent lymph nodes with long axis > 3 cm, severe or life-threatening intraoperative complications such as intra-abdominal massive haemorrhage, severe organ damage, or other technical or instrumental factors that require a conversion to open surgery.

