#### Secondary endpoints

Postoperative rehabilitation evaluation indicators: first time out of bed, first time of flatus/defecation, first time of semi-liquid diets, time of gastric tube removal, time of full removal of drainage, daily drainage volume, postoperative pain and the dosage of non-prophylactic analgesic drugs, postoperative blood transfusion volume, and postoperative hospitalization stay.One-year postoperative life quality: assessed using the European Organization for Research and Treatment of Cancer (EORTC) core 30-item Quality of Life Questionnaire for cancer patients (QLQ-C30) [13]. This questionnaire contains both Gastric (QLQ-STO22) [14] and Elderly Cancer Patients (ELD14) [15] modules and was developed to assess the generic and disease-specific quality of life of elderly gastric cancer patients. We will calculate summary scores from the mean of scales. Prior to calculating the mean, the symptom scales will need to be reversed to obtain a uniform direction of all scales. The summary score should only be calculated if all of the required scale scores are available (using scale scores based on the completed items, provided that at least 50% of the items in that scale have been completed.Three-year overall survival rate: overall survival is defined as the time interval from the time of the radical gastrectomy to the date of all-cause death or the last follow-up. Three-year overall survival rate will be calculated using the Kaplan-Meier Methods.Three-year disease-free survival rate: disease-free survival is defined as the time interval from the time of the radical gastrectomy to the date of the detection of cancer recurrence or the last follow-up. Three-year disease-free survival rate will be calculated using the Kaplan-Meier Methods.

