### Data collection

Table 2 displays the schematic diagram for the timeline of patient assessment and data collection. Assessment on surgical safety and postoperative rehabilitation status will be performed by research physicians and recorded by the research nurse within 30-days after the gastrectomy. The case manager will collect demographic information at baseline, conduct life quality assessment one-year postoperative, and do follow-up on survival status till three-years after the last treatment. After gathering all relevant data collected by physicians, research nurse, case manager, as well as lab tests and imageological examinations, the data manager is responsible for data storage, security, management, and quality control. Data quality will be double-checked by the research physician aperiodically to further promote data accuracy and completeness.

**Table 2 Tab2:** Schematic diagram for the schedule of enrolment, interventions, and assessments

TIMEPOINT	STUDY PERIOD						
	Enrolment	Allocation	Post-allocation				Close-out
	*-2 to − 4 weeks*	0	*1 week*	*4 weeks*	*Year 1* ^a^	*Year 2* ^a^	*Year 3* ^b^
ENROLMENT:							
Eligibility screen	X						
Informed consent	X						
Allocation		X					
INTERVENTIONS:							
*Open gastrectomy*			X				
*Laparoscopic gastrectomy*			X				
ASSESSMENTS:							
*Physical examination*	X				X	X	X
*Laboratory tests*	X				X	X	X
*Oncology assessment*	X				X^c^	X^c^	X^c^
*Geriatric assessment*	X						
*Surgical safety*				X			
*Postoperative rehabilitation*				X			
*Life quality*					X^d^		
*Survival status*					X	X	X

^a^conducted on a 3-month basis

^b^conducted on a 6-month basis

^c^conducted if recurrence is suspected

^d^conducted at the end of Year 1

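### Overall and disease-free survival are timed from gastrectomy rather than randomisation, which does not fit the promised intention-to-treat analysis; nor does the plan say whether intention-to-treat or per-protocol decides the superiority test

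*Protocol article*

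**What the plan says.** The abstract describes an "open-label, superiority design with two arms". On analysis sets, the Statistical analysis section reads: "Data analysis will be performed on both intention-to-treat and per-protocol basis". It defines the first set clearly: "Outcome data obtained from all participants will be included in the intention-to-treat analysis, regardless of protocol adherence". For the second, "in the per-protocol analysis, data of non-adherers will be excluded". It does not say which set decides the hypothesis or who counts as a non-adherer.

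Under Secondary endpoints, "overall survival is defined as the time interval from the time of the radical gastrectomy", and disease-free survival starts at the same event. Allocation comes earlier. The section on study design places it after staging and consent, Interventions allows up to one week from randomisation to surgery, and Table 2 puts time 0 at allocation.

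For the laparoscopic arm, Interventions says that "the case will be required to be converted to open surgery if one of the following happens". The triggers are bulky confluent nodes, severe intraoperative complications, and technical or instrumental factors. How a converted patient is classed in the per-protocol set is not stated.

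**The concern.** An intention-to-treat comparison needs a time zero that every randomised patient has. Radical gastrectomy is not one, because it happens after allocation and for some patients may not happen at all. Read literally, the definition turns the survival comparison into one of resected patients. This is a written endpoint rule, not a detail deferred to an analysis plan.

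The second issue concerns the primary comparison. With two unranked sets, the plan has no designated answer if they disagree. Only the laparoscopic arm can convert, and some triggers for conversion are themselves serious complications. How converted cases are classed could therefore shift the per-protocol result in one direction, and the article states that the data analysts are not blinded.

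**Working it through.** **1. Survival origin against the intention-to-treat sentence.** Take a patient who is randomised and dies before the operation. The death is an observed outcome, so the intention-to-treat sentence includes it. The survival definition measures from an operation that did not occur, so no survival time can be computed. Both statements cannot apply to this patient. The same holds for a patient who withdraws before surgery but whose vital status is known, and for one explored and not resected.

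**2. Size of the survival point.** The article gives no rate of non-resection. If 2-10% of the 180 randomised had no radical gastrectomy (assumed), 180 × 0.02 = 3.6 to 180 × 0.10 = 18 patients would lack a time origin. For operated patients, moving the origin to randomisation adds at most 7 days, and 7 / (3 × 365.25) = 0.6% of three years.

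**3. Sample size, reproduced.** Inputs from Statistical analysis: 35% in the open arm, a 19-point reduction to 16%, two-sided 0.05, 80% power. With pooled variance and no continuity correction, the mean rate is 0.255 and

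n = [1.960 × √(2 × 0.255 × 0.745) + 0.842 × √(0.35 × 0.65 + 0.16 × 0.84)]² / 0.19² = 81.4, rounded up to 82 per arm, 164 in total.

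This matches the article. Naming a primary set changes no input. Power is 83.8% with all 90 per arm analysed and 79.8% with 81 per arm after a 10% loss.

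**4. Two unranked sets.** In 200,000 simulated trials per scenario with no true effect (35% in both arms, 90 per arm), exclusions unrelated to outcome were set at 5-15% per arm (assumed). Claiming success on either set gave a type I error of 6.0-6.9%. Intention-to-treat alone gave 5.1-5.2% in the same simulations.

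**5. If converted patients were dropped.** Suppose there is no true effect, with 35% in both arms. Let c be the proportion converted and r their complication risk (both assumed). The per-protocol laparoscopic rate is (0.35 − c × r) / (1 − c), and the spurious benefit is 0.35 minus that.

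| c | r | Per-protocol rate | Spurious benefit |
|---|---|---|---|
| 5% | 50% | 0.325 / 0.95 = 34.2% | 0.8 points |
| 10% | 60% | 0.290 / 0.90 = 32.2% | 2.8 points |
| 10% | 80% | 0.270 / 0.90 = 30.0% | 5.0 points |
| 15% | 70% | 0.245 / 0.85 = 28.8% | 6.2 points |
| 15% | 80% | 0.230 / 0.85 = 27.1% | 7.9 points |

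For c of 5-15% and r of 50-70%, the chance of a false result favouring laparoscopy is 3.2-13.2%, by normal approximation, against 2.5% nominal. If r is 35%, or if conversions count as adherent, the bias from this source is zero. The intention-to-treat result is unaffected throughout.

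**The case against.** The strongest reply is that intention-to-treat is properly defined here: it keeps participants whatever their adherence and is listed first. A condensed article may leave the ranking of sets and the definition of non-adherence to the analysis plan. That largely stands, and it is why the ranking is the lesser point. It does not cover the survival origin, which the article fixes in words.

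Three stronger readings are tempting, and the document does not support them.

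- A reader might infer that patients drop out of the survival analysis selectively by arm. No sentence says unresected patients are removed, and non-resection can occur in either arm. Imaging, exploratory laparoscopy and peritoneal cytology are listed before randomisation, and Table 1 requires a resectable tumour and fitness for surgery. Few cases should arise, and no imbalance is shown.
- A reader might infer that the per-protocol result is biased towards laparoscopy. That follows only if converted patients are classed as non-adherers. Conversion is required by the protocol in the listed situations, so a converted case has arguably adhered. One trigger, technical or instrumental factors, need not mark a high-risk patient, and open-arm non-adherers would be excluded too.
- A reader might take the instruction under Data collection to "do follow-up on survival status till three-years after the last treatment" as a second faulty origin. It sets how long follow-up lasts, not where survival time begins.

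One further objection also stands. The primary endpoint is counted over 30 days from surgery, so a randomised patient who is never operated on has no window there either. Naming intention-to-treat as primary needs a rule for that patient.

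**Conclusion.** The point holds in a limited form. The stated origin for overall and disease-free survival is a post-randomisation event and conflicts with an intention-to-treat analysis of all participants. It concerns secondary endpoints, probably few patients, and a shift of at most about 7 days for those operated on. It is still a wrong definition with an easy correction.

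The lack of a ranking between the two sets is a secondary wording gap. The intention-to-treat set itself is sound. The 0.8 to 7.9 point range, against a 19-point target, shows why conversions need an explicit rule. It rests wholly on assumed conversion rates and risks, and on a classification the article does not make. No stated figure in the article is wrong on this account.

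**What to change.** - Define overall and disease-free survival from the date of randomisation, for all randomised patients in their allocated arm. State how a patient who is never resected counts for disease-free survival, and follow non-operated patients for survival over the same three years.
- State that intention-to-treat decides the superiority hypothesis and that per-protocol is supportive. Say how a randomised but non-operated patient is counted for the 30-day endpoint.
- Define non-adherence before data are seen, and state that conversions required by the Interventions section are adherent and stay in the laparoscopic arm in both sets.

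The cost is wording in the protocol or analysis plan. Allocation is already time 0 in Table 2, so its date should be on file. The only added effort is continued contact with the few patients not operated on. Sample size is unchanged.

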### Hypothesis

Laparoscopic gastrectomy is superior to open gastrectomy in terms of perioperative safety for local advanced gastric cancer patients aged 70 and above.

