### Assessment of outcomes

#### Primary endpoints

The primary endpoint is surgical safety, including complication rate, reoperation rate, readmission rate, and mortality rate within 30 days after surgery. Surgery related complications include incision complications (infection, effusion, dehiscence, poor healing), peritoneal effusion or abscess formation, hemorrhage (inside abdominal cavity, inside digestive tract), ileus, anastomotic leakage, anastomotic stenosis, intestinal fistula, lymphatic leakage, pancreatic fistula, gastroparesis, pancreatitis, lung infection, pleural effusion, urinary tract infection, renal failure, liver failure, cardio-cerebrovascular events (both lower extremities thrombosis, pulmonary embolism, myocardial infarction, arrhythmia, cerebral infarction, etc.), and others. Complications will be reported and graded according to the Clavien-Dindo classification of surgical complications.

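### Four 30-day rates are primary, each tested at an unadjusted 0.05, but only the complication rate is sized and no rule says which result proves superior safety

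*Protocol article*

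**What the plan says.** The Primary endpoints section states: "The primary endpoint is surgical safety, including complication rate, reoperation rate, readmission rate, and mortality rate within 30 days after surgery". The Methods part of the Abstract lists the same four rates. The Statistical analysis section makes it the aim of the primary analysis to "compare the between-group difference in 30-days postoperative complication rate, reoperation rate, readmission rate, and mortality rate", and adds that "Pearson’s Chi-squared tests or Fisher’s Exact tests, as appropriate, will be performed for this purpose". The same section closes with one level for everything: "All statistical analyses will be conducted in standard statistical software such as SAS and STATA with a significance level of 0.05 (two-sided").

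The Hypothesis section has a single directional claim: "Laparoscopic gastrectomy is superior to open gastrectomy in terms of perioperative safety".

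The sample-size paragraph uses one rate only. It says "the conventional open surgery group is expected to have a 30-day postoperative complication rate of 35"%, and that "a 19% decrease in the complication rate was considered as superiority of laparoscopic gastrectomy over conventional open approach", "with a type I error of 0.05 (two-sided) and a statistical power of 80"%. The result is 82 per arm (164), raised to 90 per arm (180) for dropout.

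The article gives no composite of the four rates, no ranking, no division of alpha, and no statement of how many rates must favour laparoscopy.

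**The concern.** The sizing paragraph describes a trial with one primary endpoint. The endpoint and analysis text describes a trial with four. The stated 5% error and 80% power belong only to the first.

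Two things follow:

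- **No decision rule.** The hypothesis concerns safety as a whole, but nothing connects four separate p-values to it. If complications fall and readmissions rise, the plan does not say whether the hypothesis is supported.
- **Uncontrolled error.** If the rate that carries the conclusion can be chosen after the results are known, the error is no longer 5%. The Study design section says that patients, surgeons and data analysts are all unblinded, so fixing the choice in advance matters.

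This is not detail left to an unseen SAP. The article itself fixes the four primary rates and the uniform 0.05. A SAP that named one endpoint would contradict the article. A SAP that kept all four unadjusted would not deliver the stated type I error.

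**Working it through.** **Inputs from the protocol article (Statistical analysis):** open-arm complication rate 35%; decrease of 19 points, so 16% with laparoscopy; two-sided alpha 0.05; power 80%; 82 evaluable per arm. The Background gives surgery-related mortality of 3.8–9.5%.

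**Assumed:** null rates for reoperation and readmission, because the document gives none.

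**1. Reproduce the stated sample size.** Pooled two-proportion formula, no continuity correction:

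n = [1.960·√(2·0.255·0.745) + 0.842·√(0.35·0.65 + 0.16·0.84)]² / 0.19² = (1.208 + 0.506)² / 0.0361 ≈ 81.4, so 82 per arm.

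This matches, with 80.3% power at 82 per arm. The 19% must be a difference in percentage points: read as a relative decrease (35% to 28.35%), the formula needs 768 per arm. The stated error and power are therefore those of a single test on the complication rate.

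**2. Error if any one of four tests sufficed, at nominal size.**

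- Any significant difference, either direction, independent tests: 1 − 0.95⁴ = 18.5% (additive bound 4 × 0.05 = 20%).
- False superiority of laparoscopy, independent tests: 1 − 0.975⁴ = 9.6% (additive bound 4 × 0.025 = 10%), against a nominal 2.5%.

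With equally correlated normal test statistics:

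| Correlation | Either direction | Favouring laparoscopy |
|---|---|---|
| 0.3 | 17.4% | 8.7% |
| 0.5 | 15.6% | 7.8% |
| 0.8 | 11.4% | 5.7% |

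**3. Error with the planned tests.** Exact enumeration at 82 per arm, with Fisher's test when an expected count is below 5 and Pearson's otherwise. The true two-sided size of one test is 4.9% at a 35% rate, 4.9% at 10%, 4.8% at 9.5%, 2.3% at 5%, 1.3% at 3.8% and 0.8% at 3%.

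Combined under independence as 1 − Π(1 − size), with complications at 35%:

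| Assumed reoperation / readmission / mortality | Either direction | Favouring laparoscopy |
|---|---|---|
| 3% / 5% / 3.8% | 9.0% | 4.6% |
| 5% / 5% / 5% | 11.2% | 5.7% |
| 10% / 10% / 10% | 18.1% | 9.4% |

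First row, worked: 1 − 0.9510 × 0.9921 × 0.9773 × 0.9866 = 9.0%. If the three rates were as low as 2%, 2% and 1%, the figures would be 5.4% and 2.7%, close to nominal.

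**4. What the trial can show on a rare primary rate.** With the planned test at 82 per arm, power to detect a halving (an assumed effect) is about 19% from 9.5% and about 2.5% from 3.8%.

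**5. Cost of keeping four primaries.** Bonferroni at 0.05/4 = 0.0125 gives 61.8% power for complications at 82 per arm. Restoring 80% needs 116 per arm: 232 evaluable, and 232/0.9 ≈ 258 randomised.

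**The case against.** The strongest reply is that the sizing paragraph shows complications were meant as the real primary endpoint. It is the only place where superiority is given a meaning, and it names that rate alone. This stands as far as it goes, and it shows which endpoint to name. But it is a sizing statement. It does not displace the Abstract, the Primary endpoints section and the primary analysis, all of which list four rates.

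A reader might infer more than the document supports in three ways:

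- **That the plan lets any one of four significant tests prove superiority.** It does not say so. It leaves the question open, so this is a permitted reading and not a stated rule.
- **That the risk of a false claim for laparoscopy is 18.5%.** That figure counts differences in either direction. A significant excess of harm with laparoscopy would not support the hypothesis. The directional figure is about half.
- **That rare outcomes add their full 5% each.** They do not, because Fisher's test is conservative at low counts. The rarer the three outcomes, the less error they add. They also overlap, since a reoperation, for example, usually follows a complication.

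Two more points stand. This is a phase II trial meant to inform phase III trials, which softens the consequences of a wrong claim. And making three rates secondary does not by itself say how to weigh fewer complications against more deaths or readmissions. It does settle which result the formal claim rests on.

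The interim look in the section on data monitoring, auditing and interim analysis is a separate matter. None of these figures count it, and the change below would not resolve it.

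**Conclusion.** The point holds. Four rates are primary at an unadjusted two-sided 0.05, one is sized, and no rule connects the four results to the hypothesis. The sizing itself is correct for the complication rate.

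On an any-of-four reading, the error is at most about 18.5% in either direction and about 9.6% for false laparoscopic superiority (nominal 2.5%), for independent tests at full nominal size. With the planned tests at 82 per arm it is about 9–18% and 4.6–9.4%. That range assumes independence and rates of 3–10% for the other three outcomes. Positive correlation or rarer events would bring it lower. The missing success rule does not depend on any of these assumptions.

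**What to change.** In the Abstract, Primary endpoints and Statistical analysis sections, name the 30-day postoperative complication rate as the single primary endpoint and the sole basis for the superiority claim. Move 30-day reoperation, readmission and mortality to secondary safety outcomes, each reported as rates by arm and a difference with a 95% confidence interval, with no superiority claim attached. Carry the same wording into the SAP and the registration where they differ.

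The cost is wording only. No new data are needed, the sample size stays at 180, and the stated 5% error and 80% power then describe the analysis that will be done. The downside is that a superiority claim can no longer rest on any of the other three rates. If the sponsor wants all four to remain primary, a composite or a multiplicity rule must be defined and the trial re-sized; under Bonferroni that means about 258 patients in place of 180.
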